### Participants

Sixty right-handed patients will be selected, aged between 18 and 60 years, who have been diagnosed with stroke in the left subcortical ischemic of the middle cerebral artery territory; according to the International Classification of Diseases (ICD-10) and whose data have been obtained by computerized tomography or magnetic resonance. The occurrence of the injury within a 6 to 12 month period will be considered chronic [19]. Only those patients referred for cognitive rehabilitation based on the clinical diagnosis by the treatment team, including interviews and neuropsychological testing [20], will be included in the clinical study. The neuropsychological screen/testing will consist of the following tests [21]. The Object Learning Test [22] will be used to assess learning and short-time memory for visually presented material. The cutoff between normal and pathologic cognitive functioning is 36 points for patients ≤64 years. The Trail Making Test A [23], which will be used to assess psychomotor speed and attention, has a cutoff for normal and impaired cognitive function equivalent to 60 s. An Assessment of Stroke and other Brain Damage [24] will be used to evaluate motor apraxia, rational apraxia and visual-spatial ability. The present study will be set at 65 points for motor apraxia (lower quartile), 14 points for rational apraxia (full score), and 25 points for visual-spatial ability (lower quartile).

Exclusion criteria are as follows: inability to perform the tests due to losses in production or understanding speech; severe clinical status, assessed by the National Institute of Health Stroke Scale (NIHSS) ≥16 points [25]; severe cognitive comorbidities, diagnosed according to clinical evaluation and according to the Diagnostic and Statistical Manual of Mental Disorders, 4th. Edition (DSM-IV) [26], and supplemented by the following instruments: Montreal Cognitive Assessment (MOCA) ≤18 points [27], Dementia Rating Scale-2 (DRS-2) ≤ 124 points [28] , and the Center for Epidemiological Studies - Depression (CES-D) ≥ 16 points [29]. In addition, exclusion criteria for the use of cortical stimulation will be applied: a) use of drugs stimulating central nervous system activity; b) patients with implanted metallic or electronic devices; c) a cardiac pacemaker; d) patients who experience seizures/convulsions; and e) pregnancy.

### Intervention

A constant current stimulator (TCT Research Limited) will be used using electrodes of 5 × 5 cm^2^ embedded in saline (0.9 % NaCl) and application of 2 mA current for 20 minutes. The protocol is identical for placebo stimulation, but the current will stop after 30 seconds from the start of stimulation, a blinding method used in several previous studies [1, 15].

The positioning of the electrodes follows the 10–20 electroencephalogram (EEG) system model. The cathode will be positioned in the right supra-orbital region (contralateral to vascular injury), while the anode will have the following provision in the left hemisphere: group 1 (dlPFC), F3 position [30]; group 2, cingulo-opercular network (CON)-anterior insula/frontal operculum, the intersection point between T3-Fz and F7-Cz [31, 32]; and groups 3 and 4, M1 position [33].

All experiments will be conducted at the same time of day (afternoon shift), including stimulation and evaluation, to avoid possible circadian cycle influences.

### Procedures

The primary outcome of the study will be the Dysexecutive Questionnaire (DEX) [34], composed of 20 subtests, standardized, with total score ranging from 0 to 80 points, applied to the patient and a family member. The issues involve disturbances in executive functions such as emotional or personality, motivational, behavioral and cognitive changes. It is an instrument with ecological validity confirmed for patients with brain injuries and may provide important information on executive functions with implications for cognitive rehabilitation [35].

Secondary outcomes will be: the Semantic Fluency Test (FAS), which assesses the recall of words that begin with a certain letter and category fluency for the generation of words in a semantic class [36]; Go-no go, which tests self-monitoring, inhibition, initiation and cognitive flexibility [37]; Wechsler Intelligence Scale for Adults (WAIS), in the subtests of digit symbol coding, matrix reasoning, comprehension and letter-number sequencing for evaluation of executive functions [38]; Rey Auditory Verbal Learning (RAVLT) test that measures recent memory, learning, interference, retention and recognition memory [39]; Letter Comparison and Pattern Comparison Tasks [40].

### Safety

To control adverse effects, reports of patients with feelings/sensations of itching, tingling, burning, headache or other discomfort (1 none, 2 mild, 3 moderate, or 4 strong) will be recorded, along with whether this effect could be related to stimulation on a Likert scale; 1 (no relation) to 5 (strongly related).

If any damage/injury occurs to the participant, he or she will be offered medical assistance/treatment, physiotherapy and psychological care without any onus or cost to the participant.

### Statistical analysis

To determine the number of participants in each group, we will apply the proposed criteria for clinical trials. As observed in previous studies using the DEX for cognitive evaluation, we found that the average obtained by individuals with cognitive decline (without presence of dementia) undergoing rehabilitation protocols lies in a range of 15 to 17 points, with a deviation-pattern of 5.0 to 8.0 points [41–43]. The minimal importance difference will be considered based on the variation of the standard error of measurement approach, considering 1 for a small effect, 1.96 for a moderate and 2.77 for a large effect [14]. From these criteria, considering 90 % power and taking into account possible dropouts, we calculate a final sample size of 90 participants. A significance level of *P* <0.05 will be considered.

An analysis of intention to treat will be used, and sensitivity analysis will be performed with different allocation procedures to verify the strength of the data. The best strategy resulting from the comparison of the following methods will be chosen: last observation carried forward, complete-case analysis, likelihood-based methods and multiple imputation.

For the primary endpoint, we will use a mixed linear model. We will model the change in cognitive performance according to the DEX using the covariates of time, group and interaction between treatment and time. The covariance with repeated measures and for each patient will also be measured. For secondary outcomes, repeated measures analysis of variance (ANOVA) will be used in which the dependent variable is the performance in each cognitive test and the independent variables are group (dlPFC, CON, M1, or sham), treatment time (baseline/initiation, week 2 and follow-up) and interaction group × treatment time. If necessary, post-hoc comparisons using Bonferroni correction will be made.

Deleterious and adverse cognitive effects will be calculated in terms of the proportion in each group and in each period, and will be analyzed by the Fisher exact test.

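### The missing-data method is to be the best of four after comparing them, with no criterion and no blinding of the choice, so the primary analysis is not uniquely prespecified

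*Protocol article*

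**What the plan says.** All the relevant text is in the protocol article, Statistical analysis.

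- Analysis set and sensitivity analysis: "An analysis of intention to treat will be used, and sensitivity analysis will be performed with different allocation procedures".
- Choice of missing-data method, in the next sentence: "The best strategy resulting from the comparison of the following methods will be chosen". The list that follows is "last observation carried forward, complete-case analysis, likelihood-based methods and multiple imputation".
- Primary model, in the next paragraph: "For the primary endpoint, we will use a mixed linear model", with terms for time, group and their interaction.
- Error level: "A significance level of *P* <0.05 will be considered". Sidedness is not stated, and no adjustment is made for a choice among methods.

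No other section makes one missing-data method primary. Missing data are expected: the Design section defines attrition, the Discussion foresees withdrawals, and the sample-size text allows for dropout without giving a rate.

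**The concern.** The article does more than leave a detail open. It states a rule: compare four methods, then choose one. Three things follow.

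1. **The criterion is undefined.** Observed data can show whether dropout depends on recorded scores, which helps to judge complete-case analysis against likelihood or imputation methods. They cannot show whether missingness also depends on the unseen values. Without a stated criterion, the estimates and P values are the most visible things to compare.
2. **Robustness checks become candidates for the main result.** Sensitivity analyses are meant to test a fixed primary result. Here any of the four may become that result.
3. **The estimand and population may change.** Complete-case analysis drops randomised patients, against the intention-to-treat analysis announced just before. LOCF and complete-case analysis generally need stronger, more restrictive assumptions than likelihood methods or multiple imputation. The choice therefore affects what is estimated as well as the P value.

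The trial is small, so a few dropouts could move a result across the 5% line.

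**Working it through.** **Inputs from the article.** Significance level 0.05 (two-sided assumed); four candidate methods; four arms in equal ratio. The number of patients is given in two ways: "Sixty right-handed patients will be selected" in Participants, and "taking into account possible dropouts, we calculate a final sample size of 90 participants" in Statistical analysis. These give 60/4 = 15 and 90/4 = 22.5 per arm, so 15 and 22 were used.

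**Inputs assumed, because the article does not give them.** Correlation 0.6 between visits; dropout at T2 of 10%, 20% or 30%, either completely at random (MCAR) or dependent on the observed T1 change (MAR), with the same mechanism in every arm. In the MAR runs the stated rate applies at average T1 change, so the overall rate is somewhat higher.

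**Step 1: the plan's figure.** One test fixed in advance gives 1 - (1 - 0.05) = 0.05, as stated.

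**Step 2: outer limits for a free choice among four.** Independent tests: 1 - 0.95^4 = 0.185. Sum bound: 4 x 0.05 = 0.20. The four methods share most of their data, so neither limit should be approached.

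**Step 3: simulation under no treatment effect.** DEX at T0, T1 and T2 was drawn from a normal distribution. All four methods tested the same quantity, the change from T0 to T2:

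- LOCF and complete-case by analysis of variance;
- likelihood by a Wald test for monotone missing data;
- multiple imputation with 20 imputations and Rubin pooling.

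Runs per row were 4,000 (four arms of 15), 3,000 (two arms of 15) and 2,500 (four arms of 22). The largest Monte Carlo standard error at 5% is sqrt(0.05 x 0.95 / 2,500) = 0.0044.

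| Arms x n | Dropout | Each method alone (%) | Most favourable of four (%) | Most favourable without LOCF (%) |
|---|---|---|---|---|
| 4 x 15 | 10% MCAR | 4.5-5.0 | 6.85 | 5.92 |
| 4 x 15 | 10% MAR | 4.8-5.5 | 7.62 | 6.18 |
| 4 x 15 | 20% MCAR | 4.7-5.1 | 7.72 | 6.45 |
| 4 x 15 | 20% MAR | 5.0-5.5 | 9.05 | 7.32 |
| 4 x 15 | 30% MCAR | 4.5-5.3 | 8.30 | 6.22 |
| 4 x 15 | 30% MAR | 4.7-5.5 | 9.10 | 6.98 |
| 2 x 15 | 10% MCAR | 4.7-5.3 | 6.57 | 6.00 |
| 2 x 15 | 30% MCAR | 4.6-5.1 | 7.40 | 6.03 |
| 4 x 22 | 10% MCAR | 5.2-5.4 | 7.48 | 6.40 |
| 4 x 22 | 10% MAR | 4.5-5.2 | 7.32 | 5.80 |
| 4 x 22 | 30% MCAR | 4.8-5.1 | 8.12 | 6.32 |
| 4 x 22 | 30% MAR | 4.0-4.4 | 8.12 | 5.92 |

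Each method fixed in advance holds close to 5%. The most favourable of four rejects in 6.6-9.1%.

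**Step 4: second check.** A separate like-for-like simulation with three methods (LOCF, complete-case, multiple imputation), all on the change score, gave about 6.2%, 7.7% and 8.2% at 10%, 20% and 30% dropout. Together the two checks support roughly 6-9%.

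**Step 5: why the same change score matters.** Setting a baseline-adjusted test against a change-score test, and taking the smaller P value, rejects in about 7% with no dropout at all. That excess comes from mixing estimators and is not due to missing data. It is excluded from the figures above.

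**Step 6: when the inflation is nil.** With no missing data the methods analyse the same values and there is nothing to choose. With a choice made blind to group, selection cannot favour one arm, so the chosen test keeps its level.

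**The case against.** The strongest reply is that the article never says the choice is made on results. It speaks of comparing methods. The comparison could concern the missingness pattern, the amount of dropout or the plausibility of each model, judged blind to group, and a SAP not shown may say so. This stands in part. A reader might infer that the type I error of this trial is inflated as a matter of fact. The text does not support that; it supports only that selection on results is permitted. Nor is the article merely silent: it states a selection rule without a criterion or safeguard.

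A reader might also infer that the rule contradicts the mixed linear model. It does not. A mixed model can be fitted to carried-forward, completer or multiply imputed data, and the disputed sentence follows directly on the sensitivity-analysis sentence, so it may concern only that layer. What remains is an ambiguity: one cannot tell which data handling gives the primary result.

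The phrase about varying allocation procedures could be taken to mean that patients are moved between arms. It is more probably a slip for imputation procedures, and it is no evidence of selection on results.

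Finally, the dropout rates and the correlation are assumptions, and the size is moderate. Without LOCF among the candidates, the range falls to 5.8-7.3%.

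**Conclusion.** The point holds in a conditional form. As written, the article does not uniquely prespecify the primary analysis, permits selection on results, and allows complete-case analysis to displace intention to treat. If the most favourable result were taken, the type I error would be roughly 6-9% instead of 5%, under assumed dropout of 10-30%, an assumed visit correlation of 0.6, the same dropout mechanism in all arms, and one common change-score estimand. It would not come near the outer limits of 18.5% or 20%. The size was similar at 15 and 22 per arm, so the disagreement between 60 and 90 patients does not affect this point.

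**What to change.** In Statistical analysis:

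1. Delete the sentence "The best strategy resulting from the comparison of the following methods will be chosen" with its list.
2. State that the primary analysis is the mixed linear model already named, fitted by likelihood to all randomised patients in their assigned arm, using every available DEX assessment.
3. Label multiple imputation, complete-case analysis and LOCF as sensitivity analyses that are reported beside the primary result and cannot replace it.
4. Clarify the wording in "sensitivity analysis will be performed with different allocation procedures to verify the strength of the data"; imputation procedures are probably meant.

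A missing-not-at-random shift within the multiple imputation is optional. The Trial status section reports recruitment in progress, so the change should be dated and made before unblinding.

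The cost is a few sentences. The same analyses are run, and neither the sample size nor the visits change.

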**Fig. 1 Fig1:**
[figure not shown]
Flow chart of study. ASB: Assessment of Stroke and other Brain Damage; CES-D: Center for Epidemiological Studies-Depression; CON: cingulo-opercular network; DEX: Dysexecutive Questionnaire; dlPFC: dorsolateral prefrontal cortex; FAS: Semantic Fluency Test; DRS-2: Dementia Rating Scale-2; LCPCT: Letter Comparison and Pattern Comparison Tasks; M1: primary motor cortex; MOCA: Montreal Cognitive Assessment; NIHSS: National Institute of Health Stroke Scale; OLT: Object Learning Test; RAVLT: Rey Auditory-Verbal Learning Test; tDCS: transcranial direct current stimulation; TMT: Trail Making Test; WAIS: Wechsler Adult Intelligence Scale

The method of randomization will be 1: 1: 1: 1, with interchange between blocks generated by an online program (random.org). Concealed allocation will be used with numbered, opaque-sealed sequential envelopes so that the person responsible for allocation will not be in contact with patients or with the work of others. All examiners will be blind to the type of treatment the patient is receiving (site of stimulation) and other assessments that will be carried out. The efficiency of the masking/blinding mechanism will be evaluated at the time of the last interview with the evaluators. They will state what region they believe the patient received stimulation in. Patients will also be blinded with a masking evaluation carried out on the last post-test where they will try to guess in which region stimulation was applied: the main (dlPFC) or secondary area (CON) of cognitive control, the motor control region (M1) or sham stimulation.

Attrition will be considered when a) three alternating or two consecutive absences; b) presence of cognitive comorbidities throughout the trial; c) loss during follow-up. There will be adherence strategies administered such as being able to make up an absence the following week, and offering flexible schedules and frequent contact through phone calls confirming dates of procedures and reinforcing the importance of treatment compliance.

The study was approved by the Health Sciences Centre Ethical Committee (#30163714.0.0000.5188) and is governed according to the principles of the Declaration of Helsinki. To conduct the study, the informed consent of each participating patient will be collected. The protocol follows all the recommendations of the Standard Protocol Items: Recommendations for Interventional Trials Statement (SPIRIT) 2013 [18].

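### The four named missing-data strategies, in their usual forms, cannot show the effect of patients lost after an unrecorded decline, a loss that one limb of the attrition rule may create

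*Protocol article*

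**What the plan says.** In the protocol article, Statistical analysis, three statements matter:

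- The analysis set: "An analysis of intention to treat will be used".
- A robustness aim: "sensitivity analysis will be performed with different allocation procedures to verify the strength of the data".
- The handling of missing data: "The best strategy resulting from the comparison of the following methods will be chosen", followed by the list "last observation carried forward, complete-case analysis, likelihood-based methods and multiple imputation".

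The primary model for the DEX contains time, group and their interaction.

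The attrition rule stands in the Design section, after the flow chart. It has three limbs: absences ("Attrition will be considered when a) three alternating or two consecutive absences"), "b) presence of cognitive comorbidities throughout the trial", and loss during follow-up. The Participants section excludes at entry "severe cognitive comorbidities, diagnosed according to clinical evaluation" and under the DSM-IV, supplemented by the MOCA, DRS-2 and CES-D.

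The article gives no dropout rate. It does not say whether the DEX is still collected once a patient counts as attrition.

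**The concern.** A check on missing data is informative only if some of the analyses relax the assumption in doubt. Here the doubtful assumption is that lost patients resemble patients who stayed. Severe cognitive comorbidity is screened out at entry, so a patient who meets the second attrition limb later has probably worsened since entry. The DEX covers emotional, motivational, behavioural and cognitive disturbance, so the reason for loss may be tied to the primary outcome. The instruments behind the comorbidity diagnosis are not terms in the primary model, which therefore does not condition on that reason.

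If one arm loses more such patients, its DEX result can look too good. Similar estimates from all four strategies could then be read as reassurance that they do not give.

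**Working it through.** **Inputs from the article.** DEX SD 5.0 to 8.0 (Statistical analysis). Assessments T0, T1 and, after one month, T2 (Design). Sixty patients in four equal arms, 60/4 = 15 per arm; Statistical analysis says 90 instead, but the bias below does not depend on this. The article has no missing-data figure to reproduce.

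**Assumed, because the article does not give them.** Loss rates, size of decline, correlation between visits, and that a higher DEX is worse. The last matters only for the sign.

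**1. What each strategy assumes in its usual form.**
- LOCF: no change after the last recorded score.
- Complete case: retained patients represent the lost ones.
- Likelihood-based methods and standard MI: a lost patient follows retained patients with the same recorded data.

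**2. Decline after the last recorded DEX.** Let pA and pB be the proportions lost through decline, s the shift, and let there be no effect in completers. Then hidden difference = (pA − pB) × s.

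| Loss | SD | Shift | Hidden difference |
|---|---|---|---|
| 20% v 7% | 8 | 8 | 0.13 × 8 = 1.04 |
| 30% v 10% | 8 | 8 | 0.20 × 8 = 1.60 |
| 20% v 7% | 8 | 4 | 0.13 × 4 = 0.52 |
| 30% v 10% | 8 | 4 | 0.20 × 4 = 0.80 |
| 20% v 7% | 5 | 5 | 0.13 × 5 = 0.65 |
| 30% v 10% | 5 | 5 | 0.20 × 5 = 1.00 |

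No trace of the decline is in the recorded data, so every listed strategy has expectation 0. Simulation agrees (15 per arm, SD 8, shift 8, correlation 0.7, 3,000 trials): all four return −0.05 to −0.08 in the first row and −0.04 to −0.06 in the second. A run with 400,000 per arm gives −0.01 and 0.03 to 0.04.

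**3. The same decline partly or fully visible at T1.** Let f be the visible fraction. LOCF returns (pA − pB) × f × s. Under equal correlation r between visits, likelihood/MI gives T1 the weight r/(1 + r) = 0.7/1.7 = 0.41. Complete case stays at 0. For 20% v 7% and s = 8:

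| f | Truth | LOCF | Likelihood/MI | Complete case |
|---|---|---|---|---|
| 1 | 1.04 | 1.04 | 0.43 | 0 |
| 0.5 | 1.04 | 0.52 | 0.21 | 0 |

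Simulation with 15 per arm gives 1.02, 0.41 and −0.02 (simulated truth 1.01) for f = 1, and 0.54, 0.23 and 0.02 (simulated truth 1.07) for f = 0.5. The methods now separate, and LOCF is right when the decline is fully visible and persists.

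**4. Loss driven by the score itself.** Assumed mean 16, SD 8, correlation 0.6, 300,000 per arm; T2 may be lost if the DEX has worsened by more than 5 points. Negative differences favour active stimulation.

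| Loss depends on | Loss active / sham | Truth | LOCF | Complete case | Likelihood/MI |
|---|---|---|---|---|---|
| unseen T2 | 5% / 19% | −3.0 | −2.41 | −1.43 | −1.77 |
| unseen T2 | 11% / 0% | −3.0 | −3.62 | −4.37 | −4.02 |
| unseen T2 | 19% / 10% | 0 | −0.45 | −1.23 | −0.99 |
| recorded T1 | 5% / 19% | −3.0 | −3.57 | −2.21 | −2.99 |

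In the first three rows all methods lie on the same side of the truth, by about 0.4 to 1.6 points, but they do not agree with each other: in the first row they spread over 2.41 − 1.43 = 0.98. In the last row likelihood/MI is unbiased, and LOCF and complete case err in opposite directions.

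**5. Equal loss.** With 19% lost in each arm through unseen T2 worsening and no true effect, the between-arm error is at most 0.01. Change within an arm is still biased, by −0.9 (LOCF) to −2.2 (complete case).

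**6. Does a shift help?** In the first two rows of step 2, MI with a matching shift of 8 points returns 0.96 (truth about 1.04) and 1.55 (truth about 1.60).

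**The case against.** A reader might infer that the four methods always err together, that their comparison can never reveal such loss, or that the attrition rule removes decliners from the data. The documents support none of these.

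- **The mechanism is chosen.** Step 2 places the whole decline at an unseen visit, which forces every method to 0. Steps 3 and 4 show that the methods diverge when T1 carries the decline, and that likelihood/MI can be valid. This stands, and it limits the claim to decline after the last recorded DEX.
- **The link to decline is inferred.** It rests on one of three limbs read with the entry exclusions. The comorbidity screen also includes depression. No rate is given. The article plans intention to treat and nowhere says that DEX collection stops; if the DEX is still measured, the mechanism disappears. This stands as a limit on certainty.
- **The method families are broad.** Pattern-mixture models are likelihood-based, and delta-adjusted MI is still MI. A condensed article may leave such detail to the full protocol or analysis plan. This stands in part: the claim concerns the usual forms. But the article itself fixes the list, and it signals no departure from missing at random.
- **Two sentences are being joined.** The robustness aim belongs to a sentence about varying allocation procedures; the four methods follow as candidates for a best strategy. No text says that agreement will be called robust. This stands, so the point is a caution about how agreement may be read, not a misstatement by the article.
- **The bias is small beside the noise.** At 15 per arm, 20% v 7% is about 3 v 1 patients, and 1.04 points is under half the standard error of 2.32 found in simulation. This is true, but a sensitivity analysis is meant to show whether a systematic error of that size could change a conclusion.

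**Conclusion.** The concern holds in a conditional form. The article names four strategies that, in their usual forms, do not allow a lost patient to be worse than a comparable completer, while one limb of its attrition rule may produce just such losses. If the decline follows the last recorded DEX and loss differs between arms, the four can agree and all miss a difference of about 0.5 to 1.6 points (SD 8, shift 4 to 8, loss 20% v 7% or 30% v 10%). The rates, shift and correlation are assumptions; only the SD range is the article's. The bias may favour or disfavour active stimulation, depending on which arm loses more decliners. This is a worthwhile, inexpensive improvement and does not show that the primary analysis is invalid. How the best of the four is to be chosen is a separate matter: naming one in advance would leave this gap open.

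**What to change.** In Statistical analysis, add a missing-not-at-random sensitivity analysis of the DEX by delta-adjusted multiple imputation. Shift the imputed scores of patients lost to attrition towards worse values, over a prespecified range from 0 up to the planning SD (5.0 to 8.0 points in the article), with the shift allowed to differ by arm. Report the shift at which the dlPFC v CON and the active v sham conclusions change. State that agreement among the four listed methods will not by itself be taken as evidence of robustness; LOCF and complete-case results may still be shown.

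The cost is a few lines of text and some programming, with no new patients or data. The downside is that results may be reported as less robust than agreement among the four would suggest.

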**Methods/Design:**

Sixty patients who suffer from chronic strokes will be randomized into one of four groups: dorsolateral prefrontal cortex, cingulo-opercular network, motor primary cortex and sham stimulation. Each group will receive transcranial direct current stimulation at an intensity of 2 mA for 20 minutes daily for 10 consecutive days. Patients will be assessed with a Dysexecutive Questionnaire, Semantic Fluency Test, categorical verbal fluency and Go-no go tests, Wechsler Adult Intelligence Scale, Rey Auditory-Verbal Learning Test, Letter Comparison and Pattern Comparison Tasks at baseline and after their tenth stimulation session. Those who achieve clinical improvement with neurostimulation will be invited to receive treatment for 12 months as part of a follow-up study.

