## Methods/Design

### Design

A clinical double-blind, randomized, controlled trial will be performed involving patients with chronic stroke, randomly assigned to four groups: Group 1) active tDCS in fronto-parietal region (dlPFC); Group 2) active tDCS in the cingulo-opercular region-CON (anterior insula/frontal operculum); Group 3) active tDCS in the primary motor cortex (M1); and Group 4) sham tDCS in M1. This region was used as a place of active and placebo control.

Initially, all participants will undergo 10 consecutive daily sessions of neurostimulation (excluding weekends). Evaluations will be conducted pre- and post-test (T0 and T1, respectively). After 1 month, the participants will be checked to see who attained clinical improvement with treatment: that is, those patients who had a final score (T2) on the Dysexecutive Questionnaire (DEX) greater than at least 2.77 standard error of measurement compared from their baseline/initial testing [14]. Those who have an adequate response will be invited to receive treatment for 12 months. In this period of follow-up, the stimulation sessions will be applied twice monthly, for 5 consecutive days. This model is similar to another that has already been applied/used by other authors with positive results in a study involving tDCS for treatment of depression in order to assess whether the benefits of regularly performed neurostimulation continue in the long term [15]. Adverse effects will be computed periodically to prevent possible deleterious effects (see Fig. 1, which demonstrates the flow of the study). Previous studies have demonstrated that tDCS induces minimal discomfort sensations, such as mild tingling and itching sensations under the electrodes, predominantly in the first few seconds of the tDCS [16, 17].

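### The primary DEX model does not adjust for baseline DEX: the planned contrast is valid, but less precise than it could be, by an amount that depends on a correlation the article does not give

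*Protocol article*

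**What the plan says.** The Statistical analysis section describes the primary endpoint model in three steps. The response is introduced with "We will model the change in cognitive performance according to the DEX". The terms are given as "using the covariates of time, group and interaction between treatment and time". Within-patient dependence is covered by "The covariance with repeated measures and for each patient will also be measured", with no structure named.

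The section does not say whether the response is a computed change score or the DEX value at each visit with T0 included. For the secondary tests, analysed by repeated measures ANOVA, baseline is explicitly a level of the response: "treatment time (baseline/initiation, week 2 and follow-up". A baseline DEX value is planned for the trial in any case. The Design section states "Evaluations will be conducted pre- and post-test (T0 and T1, respectively", and adds a T2 DEX score at one month.

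No correlation between baseline and later DEX is given. Trial size is stated in two ways. The abstract has "Sixty patients who suffer from chronic strokes will be randomized into one of four groups", and Participants has "Sixty right-handed patients will be selected". The sample-size paragraph has "we calculate a final sample size of 90 participants".

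**The concern.** Randomisation makes the true baseline means of the four arms equal. A model that lets the arms differ at baseline spends information on a difference known to be zero, and then subtracts that estimated difference in full from the follow-up difference. Write D for the observed baseline difference between two arms. With equal SDs at both visits, the follow-up difference is expected to carry rho × D of it. The change-score contrast subtracts D, so given D it is displaced by −(1 − rho) × D. Over repeated randomisations D averages to zero, so there is no bias, but the displacement adds variance.

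At stake is the precision of the pairwise comparisons, including dlPFC against CON, in a four-arm trial with small arms. The unclear response also matters, because it determines which model term is the treatment effect.

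**Working it through.** **The plan's own figure.** No figure in the article bears directly on this point. The only design figure, 90 participants at 90% power, cannot be reproduced: the standard error of measurement (SEM) in points, the SEM multiple used, the dropout rate and the test are not stated. One arbitrary choice comes close. Taking 1.96 SEM and an assumed reliability of 0.75, the difference is 1.96 × √(1 − 0.75) = 0.98 SD. Then n = 2 × (1.960 + 1.282)² / 0.98² ≈ 21.9, or 22 per arm and 88 in all, before dropout. So the size calculation does not reveal what correlation or analysis was assumed.

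**What the listed terms estimate.** Time is taken as categorical.
- *T0 is a response.* With a full group-by-time mean structure and complete data, the fitted cell means are the raw means. The interaction from T0 is therefore the difference in mean change. In a simulated data set of 60 patients with two times, the mixed-model interaction coefficients matched ordinary least squares on the change score, with SE 0.321 in both.
- *Computed change is the response.* Baseline is again unadjusted. The group term carries the treatment effect, and the interaction tests only whether that effect differs between post-baseline visits.

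**Inputs for the precision comparison.** Arms of 15 (60/4) or 22 (90/4 = 22.5, rounded down, N = 88). SD of 5.0 to 8.0 points from the sample-size paragraph, assumed equal at both visits. Rho is assumed, 0.4 to 0.9. Residual variance is pooled over four arms.

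**Formulae, for a pairwise contrast.**
- Change score: (2/n) × 2(1 − rho) × SD².
- Baseline-adjusted: (2/n) × (1 − rho²) × SD² × [1 + 1/(N − 6)]. The bracket is the expected cost of estimating the slope.
- Ratio without the bracket: (1 − rho²) / [2(1 − rho)] = (1 + rho)/2.
- Bracket at N = 60: 1 + 1/54 = 1.0185. At N = 88: 1 + 1/82 = 1.0122.

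| rho (assumed) | (1+rho)/2 | Net ratio, N = 60 | Variance saved, N = 60 | Net ratio, N = 88 |
|---|---|---|---|---|
| 0.4 | 0.70 | 0.713 | 29% | 0.709 |
| 0.5 | 0.75 | 0.764 | 24% | 0.759 |
| 0.7 | 0.85 | 0.866 | 13% | 0.860 |
| 0.8 | 0.90 | 0.917 | 8% | 0.911 |
| 0.9 | 0.95 | 0.968 | 3% | 0.962 |

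Break-even is where (1 + rho)/2 × 1.0185 = 1, so rho = 2/1.0185 − 1 ≈ 0.96 at N = 60. Simulation at 15 per arm (10,000 trials per value) gave ratios of 0.77, 0.87 and 0.97 for rho 0.5, 0.7 and 0.9.

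**In DEX points at 15 per arm, SD 5 to 8.** At rho 0.5 the change-score SE is √(2/15 × 1.0) = 0.365 SD, or 1.83 to 2.92 points. The adjusted SE is √(2/15 × 0.75 × 1.0185) = 0.319 SD, or 1.60 to 2.55 points. At rho 0.9 the SEs are 0.82 to 1.31 and 0.80 to 1.29 points.

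**In power (noncentral t, two-sided 0.05 assumed, 15 per arm).** A contrast with 80% power under the change-score test would have 89%, 85%, 83% and 81% when adjusted, at rho 0.5, 0.7, 0.8 and 0.9.

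**The case against.** The strongest case against is that nothing here is an error. A mixed model with T0 as a repeated response is a standard analysis, its contrast is unbiased under randomisation, and it already uses each patient's baseline. The article is condensed, and further covariates may appear in a fuller document. Rho may also be high: T0 and T1 are separated by only ten weekday sessions, and the Discussion describes the constructs as stable over time. The gain could then be a few per cent.

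Most of this stands. Validity is not in question, and the size of the gain is unknown. The appeal to condensation does not remove the point, because the article lists the model's terms and that list omits baseline DEX. The remark on stability gives no number, and it does not report a T0-to-follow-up correlation of DEX.

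A reader might infer more than the article supports:
- *That the planned test is biased or ignores baseline.* It does neither.
- *That a large power gain is established.* At 15 per arm, rho 0.4 and a true difference of 0.8 SD, power would go from 50% to 65% before the slope cost. Neither rho nor 0.8 SD is in the article, which scales effects in SEM units. At the same 0.8 SD, including the slope cost, power goes from 92.6% to 94.5% at rho 0.8 and is 99.8% either way at rho 0.9.
- *That 15 per arm is settled.* It follows from 60, and the article also says 90. That conflict must be reconciled separately. The ratios are almost the same either way.
- *That adjustment is free at any correlation.* It costs a little, and above about 0.96 at N = 60 it no longer pays.

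**Conclusion.** The point holds as one about efficiency and clarity. As listed, the primary model leaves DEX unadjusted for its baseline on either reading of the response, and the reading determines whether the interaction or the group term is the treatment effect. The planned contrast is valid, but less precise than a baseline-adjusted one for any rho below about 0.96 at N = 60. The net saving in variance runs from about 29% at rho 0.4 to about 3% at rho 0.9. These figures rest on an assumed rho, equal SDs at the two visits, equal arms and complete data. The change is worth making because the data are already being collected and the cost is small, but the result does not depend on it for its validity.

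**What to change.** State the response explicitly as DEX at the post-baseline visits (T1 and T2). Fit arm, visit, arm × visit, baseline DEX and baseline DEX × visit, and name the arm contrast and visit that form the primary test. Alternatively, keep T0 as a response and use a longitudinal model that constrains the arms to a common baseline mean. The two are close but not identical: they treat missing baseline values differently, so one should be chosen in advance. The article reports recruitment in progress; the choice should be fixed before unblinding.

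The secondary tests can be adjusted for their own baselines in the same way. That replaces the repeated measures ANOVA, so it is a somewhat larger edit than the one to the primary model.

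Cost: one degree of freedom per visit and about 2% of variance at N = 60 (1/54). No new data, visits or patients are needed.
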